### Data collection

The baseline assessment will be performed after randomisation. Basic information including sex, age, race, and diagnosis will be recorded retrospectively. Concerning feasibility and safety, complete blood counts, hepatic and renal function tests, and biochemical tests will be performed on the day before the operation. Ultrasonography or upper abdominal computed tomography (CT) will be performed before the operation to confirm IH biliary dilation caused by obstruction.

Patients will undergo an examination of their bilirubin levels on days 1 and 3 postoperatively to evaluate the efficiency of the operations. Upper abdominal CT will be performed postoperatively to clarify the position of the stent. Technical success is defined as successful stent placement, and clinical remission is defined as a decrease in the serum bilirubin level to less than 75% of preprocedural values within 30 days after stent placement.

Adverse events at any time will be recorded and classified as post-procedure (up to 14 days) and late (any time after 14 days) and graded according to the American Society for Gastrointestinal Endoscopy lexicon’s severity grading system [16].

Stent patency is described by time to stent dysfunction needing re-intervention. The criteria for stent dysfunction are as follows: (1) cholangitis, (2) 50% increase in bilirubin from the lowest level post-index procedure, (3) 20% increase in bilirubin from the lowest level post-index procedure and evidence of obstruction on imaging, and (4) endoscopic or radiological re-intervention confirming stent blockage or migration.

Additionally, hospitalisation data including the length of hospital stay and total hospitalisation expenses will be recorded. The schedule of enrolment, interventions, and assessments is shown in Fig. 2.

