### Primary endpoints

The primary endpoint is the efficiency of HGS and AG described by technical success and clinical remission rates. Technical success is defined as successful stent placement which is clarified by endoscopists soon after the operation. Clinical remission will be evaluated 1 month postoperatively as it is defined as a decrease in the serum bilirubin level to less than 75% of preprocedural values within 30 days after stent placement. Only patients with both technical and clinical success are considered to reach the primary endpoint.

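### The bilirubin criteria for stent dysfunction are only percentage rises from the post-procedure low, so a stent that never drained and then plateaus can be counted as patent

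*Protocol article*

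**What the plan says.** The protocol article lists stent patency among the secondary endpoints for each arm. Data collection defines it: "Stent patency is described by time to stent dysfunction needing re-intervention". Four criteria follow.

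- The first carries no bilirubin condition: "The criteria for stent dysfunction are as follows: (1) cholangitis"
- The second rests on bilirubin alone: "2) 50% increase in bilirubin from the lowest level post-index procedure"
- The third accepts a smaller rise but adds imaging: "3) 20% increase in bilirubin from the lowest level post-index procedure and evidence of obstruction on imaging"
- The fourth again needs no bilirubin change: "4) endoscopic or radiological re-intervention confirming stent blockage or migration"

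Criteria 2 and 3 give no absolute level, no reference to the preprocedural value and no link to whether the stent drained at all.

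Initial drainage is measured elsewhere. Primary endpoints defines clinical remission as "a decrease in the serum bilirubin level to less than 75% of preprocedural values within 30 days after stent placement". The same section then makes remission a required part of the composite: "Only patients with both technical and clinical success are considered to reach the primary endpoint". The article does not say what patency time a patient without remission receives.

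On timing, Data collection states: "Patients will undergo an examination of their bilirubin levels on days 1 and 3 postoperatively". Follow-up adds bilirubin at 1, 3, 6 and 12 months.

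**The concern.** A rule tied to the patient's own lowest value detects re-obstruction after drainage. It is poorly suited to a stent that never drained. There the lowest value is already high, so the threshold for dysfunction is higher still, and a patient who remains jaundiced at a steady level does not reach it.

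That patient fails the primary endpoint through clinical remission, yet can contribute patency time to the secondary endpoint as if the stent were working. The two endpoints would then describe the same stent in opposite ways, and patency would be overstated in whichever arm has such patients.

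**Working it through.** The protocol gives no figure to reproduce here, so the check applies the stated criteria to general and illustrative values. The bilirubin values, the unit (µmol/L) and the upper limit of normal are assumptions; the article gives none of them.

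**Step 1: thresholds for a patient without remission.** Let B be the preprocedural value and N the lowest post-procedure value, assumed to be reached within 30 days.

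- No remission means N ≥ 0.75 × B.
- Criterion 2 needs a later value of at least 1.5 × N, which is at least 1.5 × 0.75 × B = 1.125 × B.
- Criterion 3 needs at least 1.2 × N with imaging, which is at least 1.2 × 0.75 × B = 0.90 × B.
- The criterion 3 threshold exceeds the starting value once N > B / 1.2 = 0.833 × B.

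So without remission, criterion 2 always requires bilirubin above its preprocedural level. Criterion 3 does so too once the lowest value is above 83.3% of the preprocedural one.

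**Step 2: example.** B = 300, N = 280.

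- 280 / 300 = 93.3%, so remission fails (it needs a value below 0.75 × 300 = 225).
- Criterion 2 threshold: 1.5 × 280 = 420.
- Criterion 3 threshold: 1.2 × 280 = 336.

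A patient who stays at 300 with obstruction shown on imaging meets neither.

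**Step 3: plateau against continued rise.** Post-procedure series with lowest value 200:

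| Series | Highest / lowest | Criterion 2 | Criterion 3 (with imaging) |
|---|---|---|---|
| 200, 205, 210, 215, 220, 225 | 1.125 | not met | not met |
| 200, 205, 245 | 1.225 | not met | met |
| 200, 205, 310 | 1.55 | met | met |

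The gap is therefore confined to non-draining stents whose bilirubin levels off. A continued rise is caught.

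**Step 4: the other two criteria.** Criteria 1 and 4 need no bilirubin change. Cholangitis, or a re-intervention confirming blockage or migration, can end patency in the plateau patient. The problem remains only when neither occurs.

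**Step 5: rises within the normal range.** For an assumed upper limit of 17 to 25, a 50% rise stays normal for any lowest value up to 17 / 1.5 = 11.3 or 25 / 1.5 = 16.7. A rise from 10 to 15 therefore satisfies criterion 2 arithmetically. The endpoint, however, is dysfunction that needs re-intervention, and a patient with normal bilirubin would not ordinarily need one.

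**The case against.** The strongest case against the point has four parts.

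1. **Other safeguards exist.** Criteria 1 and 4 catch many non-draining stents, a continued rise is caught by criteria 2 or 3, and bile flow is checked with contrast before the devices are removed (Randomisation and interventions). Failure to drain also counts against the patient in the primary endpoint. All this stands and makes the gap narrow. It does not close it: patency is reported separately, and the plateau patient without cholangitis or re-intervention is still misclassified.

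2. **Handling of patients without remission may be in an analysis plan that is not shown.** That is fair for the analysis population. But the dysfunction criteria are stated in the article, and applied as written they give this patient patency time.

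3. **A reader might infer that the rule also fails at the other end**, by calling well-drained stents dysfunctional after trivial rises. The documents do not support that as a live problem, because the definition requires a need for re-intervention. What remains is a wording point: the list does not say that this requirement binds each criterion.

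4. **A reader might infer a size or a bias between arms.** The Discussion cites clinical success of 84.5% and 91% in connection with HGS, leaving 100 − 91 = 9% to 100 − 84.5 = 15.5% without it. Those are not counts of undetected non-draining stents. A fall to 80% of the preprocedural value also fails remission, some failures would meet a dysfunction criterion, and the cited studies' definition of clinical success is not shown. No separate clinical success figure is given for AG, the rule is the same in both arms, and nothing in the article compares the depth of the bilirubin fall between techniques. Neither a percentage nor a direction can be claimed.

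**Conclusion.** The point holds in a limited form. As written, the bilirubin criteria cannot recognise a stent that never drained and whose bilirubin then plateaus. Such a patient can be counted as patent despite failing clinical remission, provided there is no cholangitis and no re-intervention confirming blockage.

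The thresholds of at least 112.5% (criterion 2) and 90% (criterion 3) of the preprocedural value follow from the protocol's own percentages, given that the lowest value falls within 30 days. The 300 and 280 example is illustrative. How many patients are affected, and whether the arms differ, cannot be derived from the documents. The primary endpoint is untouched. The correction is worth making because it is cheap and removes a contradiction between two reported endpoints.

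**What to change.** 1. Keep the patency comparison in all randomised patients, on the full analysis set named under Statistical analysis.
2. Add a sensitivity analysis in which patients without technical success or clinical remission have patency time zero. Handle deaths before the 30-day assessment separately, since remission may not have been assessable in them.
3. State in Data collection that the need for re-intervention applies to criteria 1 to 3. Criterion 4 is itself a re-intervention.
4. Report any analysis restricted to patients with remission as descriptive at most. Remission arises after randomisation and is part of the primary endpoint, so such an analysis would compare selected responders.

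No absolute bilirubin level, extra imaging or repeat measurement is proposed. Adding imaging to criterion 2 would be redundant, because a 50% rise with obstruction on imaging already meets criterion 3. Confirmatory repeats are not on the stated schedule.

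The cost is wording plus one analysis on data already planned. Patency estimates become somewhat less favourable. Failed AG procedures are followed by HGS yet recorded as AG technical failures, so the sensitivity analysis gives those patients zero even if the second stent drains. It should therefore be read beside the main comparison, not in place of it.

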**Fig. 2 Fig2:**
[figure not shown]
The schedule of enrolment, interventions, and assessments

### Follow-up

The final study follow-up is scheduled at 1 year postoperatively and includes evaluation of perioperative mortality and operative complications. Follow-up assessments of the bilirubin level (total bilirubin, conjugated bilirubin, and unconjugated bilirubin) and survival status are scheduled at 1 month, 3 months, 6 months, and 1 year after the operation or until death. If follow-up information is unable to be obtained, the patient will be considered lost to follow-up, and their data will be documented accordingly.

### Statistical analysis

#### Sample size calculation

The statistical significance level is set at 5%, power of the test is set as 80%, and randomisation ratio is set as 1:1. Based on previous data, the overall success rate of EUS-HGS is 84.5–100% with complication rates of 19.6–27% [5, 17–20]. The overall success and complication rates of EUS-AG are 57–100% and 0–5%, respectively [11, 21, 22]. Using a standard sample size formula, we calculated that 74 patients per group will be needed for a total of 148 patients, after accounting for a 10% dropout rate. A provisional deadline for patient recruitment is set in July 2022; however, in case the target number of patients has not been met, the recruitment period may be extended to reach the number required (2 × 67 patients) to obtain a power of at least 0.8 (80%).

#### Statistical analysis

The full analysis set (FAS) should be as close as possible to the intention-to-treat set. On the basis of the FAS, patients assigned to the two subgroups, including the HGS and AG groups, would form the per-protocol set. The direct deletion method will be used to treat missing data.

The technical success rate, clinical remission rate, and complication rate will be presented with 95% confidence intervals and compared between the procedures using the chi-square test. Normally distributed continuous variables, such as stent patency, bilirubin level, length of hospital stays, and hospitalisation expenses will be expressed as mean ± standard deviation and will be compared using the *t* test. Concerning the secondary endpoint, Kaplan–Meier methods will be used to compute the survival analyses. The log-rank test and Cox regression analysis will be used to compare the prognosis among patients in the HGS and AG groups. Statistical analyses will be performed using SPSS® Statistics (version 25.0; IBM Corp., Armonk, NY, USA). A two-tailed distribution will be used, and statistical significance will be considered when *P* < 0.05.

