**Methods:**

This is a prospective, randomised, controlled, multicentre study with two parallel groups without masking. One hundred forty-eight patients from three hospitals who met the inclusion criteria will be randomly assigned (1:1) to undergo either EUS-HGS or EUS-AG for relief of malignant biliary obstruction. The final study follow-up is scheduled at 1 year postoperatively. The primary endpoint is efficiency, described by technical and clinical success rates of EUS-HGS and EUS-AG in patients with unreachable papillae. The secondary endpoints include stent patency, overall survival rates, complication rates, length of hospital stays, and hospitalisation expenses. The chi-square test, Kaplan–Meier methods, log-rank test, and Cox regression analysis will be used to analyse the data.

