In the HGS group, a guidewire will be inserted through the needle and placed in the common bile duct. A cystotome will be used to create a fistula, and a fully covered metallic stent will be deployed into the fistula between the stomach (or jejunum in patients with total gastrectomy) and IH bile duct. Sometimes, a bare stent will be placed through the covered stent to avoid stent migration.

Finally, all devices will be removed after confirming with a contrast agent that bile flows well through the stent or stricture. To avoid bile leakage into the peritoneum, a 7-Fr naso-biliary catheter will sometimes be placed through the metallic stent for 48 h. In cases of failed EUS-AG, EUS-HGS will be performed for being recorded as technical failed cases in the EUS-AG group. To ensure data integrity, this group of patients will still be followed up as scheduled and recorded properly.

Both EUS-HGS and EUS-AG are established procedures of biliary drainage; there are no anticipated problems that would be detrimental to our patients. We do not anticipate the need for formal stopping rules for the trial; nevertheless, severe adverse events will be recorded in a timely manner and will be supervised by the monitoring board.

A Consolidated Standards of Reporting Trials (CONSORT) checklist for this study is provided in Additional file 1. The Standard Protocol Items: Recommendations for Interventional Trials (SPIRIT) checklist is provided in Additional file 2.

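### The primary endpoint is one patient-level composite, but the analysis section tests its two components separately, names no test of the composite and does not say which result decides

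*Protocol article*

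**What the plan says.** All places are in the protocol article.

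- **Primary endpoints, closing sentence:** "Only patients with both technical and clinical success are considered to reach the primary endpoint". This is one binary outcome per patient.
- **Primary endpoints, opening sentence:** "The primary endpoint is the efficiency of HGS and AG described by technical success and clinical remission rates". The Methods part of the Abstract is similar: "The primary endpoint is efficiency, described by technical and clinical success rates of EUS-HGS and EUS-AG in patients with unreachable papillae". Both speak of two rates, and neither states the joint condition.
- **Clinical remission (Primary endpoints):** "a decrease in the serum bilirubin level to less than 75% of preprocedural values within 30 days after stent placement". The stent is not tied to the assigned procedure.
- **Statistical analysis:** the "technical success rate, clinical remission rate, and complication rate will be presented with 95% confidence intervals and compared between the procedures" by the chi-square test. The significance rule is general: "A two-tailed distribution will be used, and statistical significance will be considered when" P < 0.05. The composite is not in the list, no comparison is called primary, and no rule combines the results.
- **Randomisation and interventions:** "In cases of failed EUS-AG, EUS-HGS will be performed for being recorded as technical failed cases in the EUS-AG group". These patients continue in scheduled follow-up. No corresponding rule is given for a failed EUS-HGS.

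**The concern.** The article states an endpoint and states the tests, and the two do not match. Someone following the analysis section to the letter would produce two efficacy p-values and none for the outcome defined as primary. If the two disagree, nothing says which one answers the trial's question. The trial is open-label, so a deciding test left unfixed could be chosen once results are visible, or appear to have been. What is at stake is the main conclusion: whether the two procedures differ in efficacy, and in which direction.

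**Working it through.** The plan gives no figure for this point, so there is none to reproduce. The check has three steps.

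**1. Do the component tests determine the composite?**

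If remission could occur only after technical success of the assigned procedure, remission in all randomised patients would equal the composite, and the listed remission test would already be the primary test. The rescue rule breaks that identity. Take a patient assigned to EUS-AG whose procedure fails, who then receives EUS-HGS and whose bilirubin falls below 75% of the starting value within 30 days of that stent:

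- technical success: no (the article says so);
- clinical remission: yes, on a literal reading of the definition;
- composite: no.

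Remission and composite can therefore differ, and on the article's text the described route to this is in the AG group only.

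**2. Error rate if either component could carry the claim (conditional)**

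For two independent 5% tests: 1 − (1 − 0.05)² = 0.0975.

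The tests are correlated if remission is counted in all randomised patients. Simulation of 200,000 trials with identical arms, 67 per group (the number before dropout in Sample size calculation), remission 90% among technical successes (assumed) and no rescue gave this chance that at least one test is significant:

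| Technical success, both arms (assumed) | Remission counted in all randomised | Remission counted among technical successes |
|---|---|---|
| 90% | 8.4% | 9.8% |
| 85% | 7.9% | 9.7% |
| 77% | 7.7% | 9.6% |

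The composite tested alone rejected in 4.9–5.1% of the same simulated trials. If both components had to be significant, the error would be at most 5%.

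**3. Can components and composite disagree? (illustration only)**

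Inputs: technical success 93.7% and clinical success 84.5% for HGS, from the meta-analysis cited in the Discussion; 77% for AG, from the pooled case count cited there. Assumptions: the 77% is treated as technical success, although the article calls it overall success; remission after any successful stent is 0.845 / 0.937 = 0.902 in both arms; failed AG is rescued by HGS with 93.7% technical success; failed HGS never remits.

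- Composite, HGS: 0.937 × 0.902 = 84.5%.
- Composite, AG: 0.77 × 0.902 = 69.4%. HGS is better by 84.5 − 69.4 = 15.1 points.
- Remission in all randomised, HGS: 84.5%.
- Remission in all randomised, AG: 0.694 + 0.23 × 0.937 × 0.902 = 88.9%. AG is better by 88.9 − 84.5 = 4.4 points.
- Remission among technical successes: 90.2% in both arms, no difference.

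Sensitivity to the two assumptions that matter most:

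- If 77% is already overall success, the composite gap is 84.5 − 77 = 7.5 points.
- If failed HGS patients were drained with the same success, HGS remission would be 0.845 + 0.063 × 0.937 × 0.902 = 89.8% against 88.9%. The reversal disappears, but the gap of about 1 point is still far from the composite's 15.

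The three outcomes also differ in power. With remission set at 91% and the other illustrative assumptions unchanged, 67 per group gives 79% for technical success (93.7% v 77%), 56% for the composite (85.3% v 70.1%) and 12% for remission (85.3% v 89.7%).

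**The case against.** The strongest reply is that everything needed is already in the article. The endpoint is fixed per patient, it is binary, and chi-square, two-sided testing, the 5% level and 95% confidence intervals are all stated. Only a sentence joining them is absent. The article condenses a fuller protocol, and the listed rates can be read as descriptive reporting of the two elements named in the opening sentence of Primary endpoints. Much of this is fair, and it limits what can be said. It does not remove the point: the analysis section is not silent on the efficacy tests. It names them, and they are not tests of the outcome defined as primary.

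Three stronger readings are tempting, and the article does not support them.

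- **A reader might infer that the primary question has no valid test.** A chi-square test of the composite would be valid. It is simply not specified.
- **A reader might infer that the trial gives itself two unadjusted chances to succeed.** No sentence says that a win on either component is a positive trial. The only combining rule is that both must hold, at patient level.
- **A reader might infer that rescue is shown to bias remission towards AG, or to reverse the result.** The article says rescued patients are technical failures and stay in follow-up. It does not say they will be counted as remissions, and limiting remission to the assigned stent is an open reading. The reversal also depends on relabelling the cited 77% and on no failed HGS patient ever remitting.

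**Conclusion.** The concern holds as a mismatch between two stated rules: a composite primary endpoint, and an analysis that lists only its components and names none as decisive. This rests on the text alone and on no assumed rate. That the components are not interchangeable with the composite follows from the rescue rule together with the remission definition.

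The sizes are conditional. The 8–10% false-positive rate applies only if significance on either component would be claimed as a positive primary result, and its place in that range depends on a remission denominator that the article does not state. The illustration shows that the answer can move by many points, and under some assumptions change sign, with the outcome chosen. It is not a forecast. The point deserves settling before any outcome data are compared, because it governs the trial's main conclusion.

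**What to change.** In Statistical analysis, name one primary analysis: the proportion of all randomised patients, by assigned group, with both technical success of the assigned procedure and clinical remission, compared by chi-square at two-sided 5%, with a 95% confidence interval for the difference.

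Label technical success and clinical remission as supportive secondary analyses. Report remission regardless of rescue, and describe it that way. Counting failures of the assigned procedure as non-remission would make this variable identical to the composite, so the same test would appear twice.

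Align the Abstract and the opening sentence of Primary endpoints with the joint definition.

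The cost is a few sentences. No extra patients, data or visits are needed, and clinical management is unchanged.

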To date, all reports of the safety and efficiency of EUS-HGS and EUS-AG were based on observational studies and randomised controlled studies with another technology or evidence-based medicine. Ardengh et al.’s contradictory findings also appeal to the need for a further comparative study of EUS-HGS and EUS-AG. To our knowledge, ours will be the first study to compare these two EUS-BD approaches directly in a multicentre, randomised, controlled trial. The clinical economic indexes will also be compared, as they may also affect the patient’s choice.

There are limitations to the present study design. The internal biliary drainage operation is a palliative treatment for unresectable malignant biliary obstruction. The lifetime of patients included is limited, because death caused by cancer progression is inevitable. Therefore, the long patency of the stent is difficult to evaluate.

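### Stent patency, a censored time to event and a secondary endpoint, is assigned to mean ± SD and a t test, which is wrong as written

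*Protocol article*

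**What the plan says.** All places are in the protocol article.

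- **Data collection** defines the endpoint as a time to an event: "Stent patency is described by time to stent dysfunction needing re-intervention". Four criteria for dysfunction follow.
- **Follow-up** sets the limit of observation: "The final study follow-up is scheduled at 1 year postoperatively". Assessments fall at "1 month, 3 months, 6 months, and 1 year after the operation or until death".
- **Discussion**, in its paragraph on limitations, says "The lifetime of patients included is limited, because death caused by cancer progression is inevitable", and concludes that long stent patency is hard to assess.
- **Statistical analysis** puts stent patency first in a list of examples: "Normally distributed continuous variables, such as stent patency, bilirubin level, length of hospital stays, and hospitalisation expenses will be expressed as mean". The sentence goes on to pair that mean with an SD and to name the t test for the comparison between arms.
- The same section gives the methods for censored data other targets. One sentence reads "Kaplan–Meier methods will be used to compute the survival analyses". Log-rank and Cox are tied to prognosis: "The log-rank test and Cox regression analysis will be used to compare the prognosis among patients in the HGS and AG groups". Neither sentence names stent patency.
- The only rule for incomplete data in that section is direct deletion.

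**The concern.** A mean and a t test need a completed value for every patient. Patency has one only for patients whose stent fails under observation. For the others, who die or reach 1 year with a working stent, the analyst must either enter the follow-up time as if the stent had failed then, or drop them. The first choice mixes stent durability with survival. The second keeps only the stents that failed.

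The protocol has a substantive interest in this comparison. Its Discussion notes that the antegrade stent lies within the tumour, that tumour growth is the main cause of re-obstruction, and that re-intervention is harder after the antegrade technique. A patency comparison that partly measures survival would blur that trade-off.

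**Working it through.** **What can be reproduced.** The plan states no figure for stent patency, so there is none to reproduce. The check uses the plan's 67 evaluable patients per group (Sample size calculation), its 1-year limit (Follow-up) and its two-sided 5% level. Median patency and median survival are assumptions, varied below. Times to dysfunction and death are taken as exponential and independent.

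**Bias of the mean.** With hazards a = ln 2 / median patency and d = ln 2 / median survival, and λ = a + d:

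- restricted mean patency to 12 months = (1 − e^(−12a)) / a
- mean observed time (censored times averaged) = (1 − e^(−12λ)) / λ
- mean among observed dysfunctions only = 1/λ − 12e^(−12λ) / (1 − e^(−12λ))
- proportion with an observed dysfunction = (a/λ)(1 − e^(−12λ))

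For median patency 8 and median survival 5 months, a = 0.0866, d = 0.1386 and λ = 0.2253 per month:

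- restricted mean = (1 − 0.3536) / 0.0866 = 7.5 months
- mean observed time = (1 − 0.0670) / 0.2253 = 4.1 months
- dysfunctions only = 4.44 − 0.86 = 3.6 months
- observed dysfunction = 0.385 × 0.933 = 36%

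At median survival 6 months the two observed means are 4.5 and 3.8. At 4 months they are 3.7 and 3.3. Both lie below 7.5 throughout.

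**Type I error (simulation, 67 per arm, both arms with median patency 8 months).**

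| Median survival, months | t test, observed times | t test, dysfunctions only | Log-rank |
|---|---|---|---|
| 6 v 6 | 5.2% | 4.9% | 4.6% |
| 6 v 5 | about 9% | – | about 5% |
| 6 v 4 | 28.7% | 8.5% | 5.0% |
| 8 v 4 | 57.8% | 12.6% | 5.0% |

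The mechanism shows in the means: at survival 6 v 4 the observed means are 4.5 and 3.7 months although the stents are identical.

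**Power (equal survival in both arms).**

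| Median patency | Median survival | t test, observed times | Log-rank |
|---|---|---|---|
| 10 v 5 | 5 | 36% | 71% |
| 8 v 4 | 4 | 34.7% | 71.4% |
| 8 v 4 | 6 | 50.5% | 78.7% |
| 10 v 5 | 12 | 60% | 83% |
| 12 v 6 | 4 | 23.7% | 59.7% |

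Keeping dysfunctions only, power is 12%, 13% and 17% in the first three rows and 9% in the last.

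**Masking.** If median patency is 8 v 4 months and median survival 4 v 8, λ is the same in both arms (ln 2 × 3/8). The observed means are then both 3.7 months. The t test rejects in 4.9% of runs and log-rank in 77.3%.

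**The case against.** **The endpoint is secondary.** This stands. The primary endpoint is technical success plus clinical remission within 30 days, compared by chi-square. No sample-size figure depends on patency.

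**The plan already contains time-to-event methods.** The Kaplan–Meier sentence opens with a reference to the secondary endpoint, and the Abstract lists patency first among the secondary endpoints and then names Kaplan–Meier, log-rank and Cox but no t test. So part of the defect is inconsistent wording. It does not cancel a sentence that names stent patency under the t test.

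**The t-test sentence is limited to normally distributed variables.** The text offers patency as an example of such a variable, so the condition gives no way out. A rank test on the same times would not deal with censoring either.

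**A reader might infer that death cuts patency short in most patients.** The documents give no survival time and no proportion dying within a year. With median patency 8 months, death comes first in 57% at median survival 5 months but in 33% at 12 months.

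**A reader might infer that the error rate is wrong in every case.** It is not. Type I error is nominal when survival is equal, and no passage gives a survival difference between the arms. Survival is, however, itself a compared endpoint, so equality cannot be presumed. Under the deletion rule the inflation at 6 v 4 months is to about 8%, not 28%, though power is then much worse.

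**A reader might set the observed 4.1 months against the full exponential mean of 8 / ln 2 = 11.5.** With follow-up ending at 1 year, that mean cannot be estimated without extrapolation. The restricted mean of 7.5 is the fair comparator.

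**Conclusion.** The stated analysis of stent patency is wrong as written. It conflicts with the protocol's own definition, with its follow-up limit and with its remark on death. The issue concerns a secondary endpoint and does not touch the primary conclusion.

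The mean is biased downwards under either way of handling patients without dysfunction, and power is lost even when survival is equal. Type I error is inflated only if survival differs between arms, by an amount that depends on that difference. The power loss ranges from about a quarter (60% against 83%) to more than half (24% against 60%), so a flat claim that half the power is lost is not supported.

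Every size given here rests on assumed medians and on independent exponential times. If tumour progression drives both dysfunction and death, the figures would change. The contradiction in the text would not.

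**What to change.** In Statistical analysis, remove stent patency from the list of variables summarised by mean ± SD and compared by t test. State instead that it is analysed as time to dysfunction with the Kaplan–Meier, log-rank and Cox methods already planned, censoring at death without dysfunction, at loss to follow-up or at 1 year. This is a cause-specific comparison and should be described as such.

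As a descriptive supplement, report the cumulative incidence of dysfunction with death as a competing event, and note that this quantity also depends on survival. With identical stents (median patency 8 months) and median survival 6 v 4 months, it is 39% v 32% at 12 months: 0.429 × 0.912 against 0.333 × 0.956.

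The cost is a change of wording and slightly more analysis. The dates of dysfunction, death and last contact must be recorded. The article schedules survival status and bilirubin at fixed visits but does not say that a last-contact date is kept, so the case report form should be checked for it.
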